### Participants

At least 200 participants who are PLH with mild to moderate depressive symptoms will be included. Participants will be approached in 23 of the 27 HIV treatment centers throughout the Netherlands during their regular visits to the HIV nursing consultants and doctors. To be eligible to participate in the study, a participant must meet all of the following criteria: being HIV positive, exhibiting mild to moderate depressive symptoms (defined as Patient Health Questionnaire 9 (PHQ-9) [22] score > 4 and < 20), age 18 and older, having sufficient knowledge of the Dutch or English language, able to access the Internet, having an e-mail address, and available for the next 8 weeks to work on the intervention.

An eligible participant who meets any of the following criteria will be excluded from participation in the study: being in the first half year following HIV diagnosis, having severe cognitive impairments (e.g., forgetfulness), exhibiting severe depressive symptoms (defined as PHQ-9 score of 20 or higher), experiencing suicidal ideation (indicated by a score > 1 on the suicide item of the PHQ-9), showing an absence of depressive symptoms (indicated by a PHQ-9 score of 4 or lower), undergoing treatment presently by a psychologist or psychiatrist, or on antidepressants for less than 3 months or has experienced a change of type or dose of antidepressants in the past 3 months. In case of severe depressive symptoms (using the set criterion) and/or suicide ideation, patients will be referred to their general practitioner or the HIV treatment center.

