### Sample size

A power analysis was performed (with the program Power Analysis and Sample Size Software: PASS; [23]) to determine the sample size needed to assess the long-term effect of the intervention on the primary outcome depressive symptoms. Based on a medium effect size of 0.50, which proved to be realistic according to the previous pilot RCT, and assuming an alpha of .05 and a power of .80, both groups should consist of 64 participants who complete the four measurements. This sample size is also large enough to detect moderate pre-defined two-way cross-product interactions, such as the interactions of group by sex. Taking into account a dropout rate of 15 % during working on the self-help program (based on our recent studies, which included coaching [21]), at least 150 patients should be allocated to the two groups at baseline (*n* = 75 in each group). We will aim for at least 200 participants because dropout will also occur during the follow-up.

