### Statistical analyses

A two-tailed alpha of .05 will be used for significance testing. All analyses will be based on an intention-to-treat (ITT) analysis, which includes all participants who were randomized to one of the groups at the beginning of the study [47]. Baseline differences between conditions will be investigated with chi-square tests for categorical variables and ANOVAs for continuous variables.

To examine the effect of condition on the depressive symptoms at the post-tests, longitudinal multilevel regression analysis (LMRA) will be conducted [48]. A two-level model will be studied: time at level 1 and participants at level 2. The variable time will have four categories indicating the four time points (T0–T4). The baseline (T0) will be used as reference category. The independent variable is condition, the dependent variable is the score on the PHQ-9 or the CES-D, and several covariates will be included in the model (e.g., sex and age). Multiple imputation for missing data is not necessary in LMRA because it can include participants with missing data on one or more time points [48]. The existence of an effect of HIV treatment center will be investigated exploratory.

Furthermore, Cohen’s d will be calculated to indicate within- and between-group effect sizes [49]. In addition, clinically important differences for individual change in depressive symptoms will be examined. Change scores of 5 or more from the pretest to the post-tests will be considered as clinical important differences for the PHQ-9 [50].

With regard to all secondary outcomes, we will study the pre-treatment versus post-treatment changes by using the analyses described above for the PHQ-9 and the CES-D. To examine moderators of the treatment outcome, LMRA will be conducted. Potential moderators will be entered individually. Interaction effects will be investigated (e.g., time x condition x moderator). A limited number of cross-product interactions will be examined, and we will correct for multiple testing. Furthermore, the QUINT (Qualitative Interaction Trees [51]) method will be used to identify subgroups for which the intervention is most effective, by exploratory investigation of the multiple moderators.

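### Baseline depression is modelled as an outcome level, so on the natural reading the effect is a difference in change: valid, but less precise than a baseline-adjusted analysis of the same data

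*Protocol article*

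**What the plan says.** The Statistical analyses section of the protocol article describes a two-level model, with time within participants. Time is categorical with four points, and "The baseline (T0) will be used as reference category". The outcome is the PHQ-9 or CES-D score and the independent variable is condition. Sex and age are given as examples of covariates. The baseline score is not named as a covariate, and nothing is said about whether the arms may differ at T0. A condition by time term is not written out for the primary analysis. It can be inferred from two places in the same section: the moderator analysis uses a three-way term with time and condition, and the same analyses are applied to the secondary outcomes as a study of change from before to after treatment. In the Assessments section, baseline severity appears only as a possible moderator.

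The Design and Procedure sections place T0 before allocation. The Sample size section starts from an effect size: "Based on a medium effect size of 0.50, which proved to be realistic according to the previous pilot RCT". It continues: "assuming an alpha of .05 and a power of .80, both groups should consist of 64 participants who complete the four measurements". It then allows for dropout, so that "at least 150 patients should be allocated to the two groups at baseline", and sets a recruitment target of at least 200 because of losses during follow-up. It gives no SD, no baseline to follow-up correlation, and no statement of the analysis that the calculation assumed.

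**The concern.** When baseline is an outcome level and each arm has its own T0 mean, the condition by T1 coefficient compares mean changes. Chance differences between arms at T0 are then subtracted in full, although the best prediction of their carry-over to follow-up is only partial. Because T0 precedes randomisation, the arms have equal T0 means in expectation. A model that uses this fact is never less precise.

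The stake is the width of the interval for the main result and for every secondary scale analysed in the same way. The Trial status section says that recruitment is complete, so the analysis is the main remaining place to gain precision.

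**Working it through.** **Inputs.** From the Sample size section: effect size 0.50, power 0.80, 64 completers per arm, 15% dropout, 75 per arm allocated, target of at least 200. From Statistical analyses: "A two-tailed alpha of .05 will be used for significance testing". From Design: 1:1 allocation. Not given in the article, and so assumed: r (range 0.3 to 0.7) and the ratio of baseline to follow-up SD.

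**The plan's own figure.** A two-sample t-test with d=0.50, two-sided alpha 0.05 and power 0.80 needs 63.77, so 64 per arm (power 80.1% at 64). The stated figure reproduces with no baseline information. For dropout, 64/0.85 = 75.3, so 76 per arm against 75 stated, a rounding difference.

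**Variance factors** (equal SDs, complete data, in units of the single-score variance):
- post-test score alone: 1
- difference in change (free T0 means): 2(1-r)
- baseline-adjusted, or common T0 mean: 1-r²

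Efficiency of change against adjustment = (1-r²)/[2(1-r)] = (1+r)/2. A generalised least squares calculation with T0, T1 and T2, equal correlations and complete data gave exactly these factors.

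**Power if 0.50 is on the raw-score scale.** The t-test effect size is 0.50 divided by the square root of the factor. The 85 per arm is 200/2 × 0.85.

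| r | 2(1-r) | 1-r² | Efficiency | 64 per arm: change / adjusted | 85 per arm: change / adjusted |
|---|---|---|---|---|---|
| 0.3 | 1.40 | 0.91 | 65% | 66.0% / 83.7% | 78.2% / 92.5% |
| 0.4 | 1.20 | 0.84 | 70% | 72.7% / 86.5% | 84.1% / 94.3% |
| 0.5 | 1.00 | 0.75 | 75% | 80.1% / 90.0% | 90.0% / 96.3% |
| 0.6 | 0.80 | 0.64 | 80% | 88.1% / 93.9% | 95.2% / 98.2% |
| 0.7 | 0.60 | 0.51 | 85% | 95.2% / 97.6% | 98.7% / 99.5% |

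For equal precision, the change contrast needs 1/0.65 = 1.54 times the participants at r=0.3 and 1/0.80 = 1.25 times at r=0.6. It reaches 80% power when r is at least about 0.50 with 64 per arm, 0.45 with 70 (30% of 200 lost, an assumption) and 0.33 with 85.

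**Unequal SDs.** Let k be the T0 SD divided by the follow-up SD. In units of the follow-up variance, change has factor 1+k²-2rk and adjustment has 1-r². The gap is (1+k²-2rk) - (1-r²) = (k-r)², which is never negative. So adjustment is at least as precise for any k, but the loss and the power threshold both move: the change factor equals 1 at r = k/2. At r=0.4, k=0.8 gives 1+0.64-0.64 = 1.00 (power 80% at 64 per arm) and k=0.7 gives 1+0.49-0.56 = 0.93 (83%), against 0.84 after adjustment in both cases.

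**The case against.** The strongest reply is that free T0 means are inferred. The text does not write the condition by time term for the primary model, and a model with a common T0 mean would also fit its words and would already have the full precision. This stands, which is why the point is about the natural reading. The text still supports that reading: the model is described as a study of change, baseline differences between arms are to be tested, and no constraint is mentioned. The other literal reading, a condition effect with no interaction, would average in T0, where no difference is expected, and would dilute the effect.

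A reader might go further and infer that the trial is underpowered. The documents do not support that:
- The SD scale of the 0.50 is not stated. If it is already a standardised difference in change, 64 per arm gives 80% power whatever r is.
- r is not stated either. Above about 0.50, the change contrast exceeds 80% power even with 64 per arm.
- The target of 200 gives room beyond 64 per arm, although the article reserves it for follow-up losses.

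A reader might also argue that the entry restriction (PHQ-9 "score > 4 and < 20") lowers r and hence power. It may, but it may also shrink the T0 SD, which works the other way. It applies to a separate telephone screening score, and the CES-D has no entry limits. No conclusion about power can be drawn from it.

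Finally, the exact identity with a difference in mean change holds for complete data. With missing post-tests, the likelihood-based estimate departs from it, so the efficiency figures are then approximate.

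**Conclusion.** The point holds as a free improvement; it does not show an error. On the natural reading, the planned contrast is valid and unbiased under randomisation but gives up precision that the T0 data would supply. With equal SDs and complete data, its efficiency is (1+r)/2, or 65% to 80% for an assumed r of 0.3 to 0.6. With unequal SDs the loss differs in size, but baseline adjustment is never less precise.

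The figure of 64 per arm reproduces and is not shown to be wrong. Power below 80% requires three things together: d=0.50 on the raw-score scale, equal SDs, and a low r (under about 0.50 with 64 completers per arm, under about 0.33 with 85).

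**What to change.** Write out the primary model in one of two forms:
- T0 and the post-tests as outcomes, with a common T0 mean for both arms: time plus condition by post-test terms, no condition effect at T0, unstructured covariance.
- The post-tests as outcomes, with T0 score and T0 score by time as covariates.

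State that the between-arm contrasts are those at T1 and T2. T3 is collected only in the intervention arm. It may stay in the model for within-arm description, but it gives no between-arm contrast. Apply the same form to the PHQ-9, the CES-D and the secondary scales measured at T0. State also the SD scale of the 0.50 and the correlation assumed, if any, behind the power calculation.

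The cost is wording only. T0 is completed before allocation, so no new data are needed. The change should be fixed before outcomes are examined by arm.

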## Methods/design

### Design

The study is a randomized controlled trial; participants will be randomly allocated to the intervention or the control group. Stratified randomization by treatment center and sex will be conducted. Stratification by sex is conducted, as there will be more male participants in the study, and the allocation of approximately the same number of females to the intervention group as to the control group is preferred. In addition, stratification by treatment center is being conducted because the number of (included) patients will differ among the treatment centers. Approximately equal allocation to each of the groups also in the small treatment centers, is important. This will be realized by creating random number tables for each treatment center, divided by sex. Randomization will take place in blocks of 12 participants for each treatment center. Males and females will represent separate blocks, with six males and six females for each treatment center, of which half will be randomly allocated to the intervention group, and half will be allocated to the control group. Participants, coaches, and researchers cannot be blind for allocation to conditions. Participants will be allocated to one of the conditions after the pretest. The random number tables will be created by an independent researcher, and the allocation sequence will be concealed from the main researcher, who enrolls and informs participants.

The design consists of multiple measurements, one pretest, three post-tests (two in the control group), and three assessments during the intervention/waiting period. Figure 1 shows a flow chart of the study design, and the SPIRIT Checklist is presented in Additional file 1. The study is approved by the medical ethics committee of the Leiden University Medical Center (LUMC; nr. P14.091). Online informed consent will be obtained from all participants.

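### Sex, age and other time-constant covariates, entered as main effects, would hardly touch the condition-by-time effect that the model is meant to estimate

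*Protocol article*

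**What the plan says.** The Statistical analyses section plans a two-level regression, with occasions nested in participants, for the PHQ-9 or CES-D score. The T0 score is itself one of the modelled outcomes: "The baseline (T0) will be used as reference category". Condition is the independent variable, and the aim is its effect at the post-tests. On covariates the section says "several covariates will be included in the model (e.g., sex and age". Interactions with time are mentioned only for the moderator analyses. Participants with missing occasions stay in the model, without imputation.

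Four other places bear on the point:

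- Design: "Stratified randomization by treatment center and sex will be conducted".
- Sample size: "Taking into account a dropout rate of 15 % during working on the self-help program", with further, unquantified dropout expected in follow-up.
- Ethical precautions and Demographic variables and other information: referral, medication use and treatment received since the start of the study are also to be covariates.
- Table 1, footnote: T3 is not sent to the control group, so the randomised comparison covers T0 to T2.

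**The concern.** With T0 in the outcome vector, the treatment effect is read from condition by time: how much more one group changed from T0 than the other. Sex and baseline age do not vary within a person. As main effects they raise or lower all of a person's scores equally, so they cannot explain why one person changed more than another.

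Two things are at stake. If age, say, predicted change and happened to differ between groups, an effect described as adjusted for age would still carry nearly all of that imbalance. And any prognostic value of sex (a stratification factor) or age for change would go unused, although the data are collected at the pretest.

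**Working it through.** **1. The plan's own figure.** Inputs from Sample size and Statistical analyses: effect size 0.50, two-sided alpha .05, power .80. The normal approximation gives 63 per group. The two-sample t-test gives 63.77, so 64, with power 0.801. Allowing for 15% dropout, 128 / 0.85 = 150.6. The stated 64 per group and 150 in total are reproduced within rounding, and no covariate gain is built into them.

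**2. The model as naturally read.** For person i at occasion t, with condition C and time-constant covariate X:

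Y_it = α + β_t + γC_i + δ_tC_i + θX_i + u_i + e_it, with β_0 = δ_0 = 0.

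The change from T0 is Y_it − Y_i0 = β_t + δ_tC_i + (e_it − e_i0). The term θX_i has gone.

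**3. This does not depend on the covariance structure.** In complete data all information on θ sits in the weighted mean 1′Σ⁻¹Y. For any change contrast c (with c′1 = 0), cov(c′Y, 1′Σ⁻¹Y) = c′ΣΣ⁻¹1 = c′1 = 0. The estimate of δ_t is therefore unaffected by X.

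**4. Numerical check, complete data.** The data were simulated and a random-intercept model fitted by REML.

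| Condition by time | Without covariates | With sex + age main effects |
|---|---|---|
| T1 estimate | −1.7447 | −1.7447 |
| T2 estimate | −2.33695 | −2.33695 |
| SE, T0 to T2 only | 0.72912 | 0.72912 |
| SE, with T3 in the intervention arm only | 0.72419 | 0.72456 |

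The last row differs by less than 0.1%.

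**5. With dropout.** Assumed: 15% first, then 10% to 12% per later visit. The documents give only the 15%.

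- Cancellation is now approximate. In two simulated trials the T1 estimates moved from −3.301 to −3.278 and from −2.074 to −2.034. The T2 estimates moved from −2.539 to −2.549 and from −2.377 to −2.335. These are shifts of 0.01 to 0.04 points against standard errors of about 0.75 to 0.80.
- The variance ratio at T2, with versus without the covariate, was 0.997, 0.994, 0.987 and 0.977 for an assumed R² of 5%, 10%, 20% and 30% (assumed within-person correlation 0.5). The gain is about 0.3% to 2.3%.
- If dropout depends on the covariate differently by arm, the main effect matters. With a true T2 effect of −0.50 SD, the fits without and with the covariate gave −0.570 and −0.527 at R² 5%, and −0.630 and −0.526 at R² 30%. The difference is 0.04 to 0.10 SD.

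**6. What covariate-by-time terms would add.** With a term λ_tX_i, the change becomes β_t + δ_tC_i + λ_tX_i + error, and the standard error is multiplied by about √(1 − R²), where R² now refers to change. The equivalent gain in sample size is 1/(1 − R²) − 1.

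| Assumed R² for change | Gain in effective sample | On 200 participants |
|---|---|---|
| 3% | 3.1% | about 6 |
| 5% | 5.3% | about 11 |
| 10% | 11.1% | about 22 |

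As an illustration, take one simulated data set with 100 per arm, in which age and sex were assumed to act on the post-tests (1.5 points per SD of age, 2 points for sex). The T1 effect was 1.1111 (SE 0.7025) both without covariates and with main effects, and 0.9301 (SE 0.6740) with covariate-by-time terms. The shift of 0.181 is about a quarter of a standard error.

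If the covariate has the same effect at every visit, the extra terms gain nothing and cost little. In such a simulation with complete data the standard error rose from 0.1633 to 0.1635.

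**The case against.** The strongest reply is that the criticised specification is not written down. The article says neither that covariates enter as main effects only nor, in so many words, that the effect is condition by time, and a condensed article may leave such detail to the full plan. Part of this stands: main-effect entry is an inference. But the T0 reference and the aim of an effect at the post-tests point to condition by time, and the section reserves time interactions for moderators. Sex and age are also listed as moderators, so those models may contain sex-by-time and age-by-time terms. They are separate secondary analyses, with moderators entered one at a time.

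Three stronger readings are tempting, and the documents do not support them:

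- A reader might infer that these covariates adjust nothing, so that the reported effect is numerically the unadjusted one. That is exact only in complete data. The protocol expects dropout and keeps incomplete participants, so the main effects do enter the estimate and can reduce bias from covariate-related dropout.
- A reader might infer that all planned covariate adjustment is empty. Referral, medication use and treatment received arise after randomisation and vary over time, so they do not cancel. In the first simulated trial of step 4 a time-varying treatment covariate moved the T2 effect from −2.337 to −2.183 even in complete data. They raise a different question.
- A reader might infer that the planned effect is biased or the sample size wrong. Neither follows. A covariate that shifts all visits equally is already removed by the change contrast. Stratification limits imbalance in sex. The plan claims no precision from covariates.

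It also stands that nothing in the documents shows sex or age to predict change, so the size of the benefit is assumed.

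**Conclusion.** The point holds in limited form. With T0 as an outcome occasion and the effect read from condition by time, main effects of sex, age and other time-constant covariates cancel exactly in complete data and add almost no precision under the expected dropout (0.3% to 2.3% of variance at T2). They would not meaningfully correct a chance imbalance in a predictor of change. The precision forgone is about 3% to 11% of effective sample, if such covariates explain 3% to 10% of the variance in change; that range is an assumption. The conclusion rests on main-effect entry, which is inferred. It is an efficiency and reporting matter that should be settled, not a flaw that invalidates the analysis.

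**What to change.** Keep the main effects, and add the interaction with time for each pre-randomisation covariate, at least sex and age. Alternatively, model only the post-tests as outcomes given T0, with these covariates as main effects, which then do act on the contrast. State which model supplies the reported effect, and describe the effect as covariate-adjusted only on that basis.

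The second option also changes how baseline depression is handled, which brings its own gain. With within-person correlation ρ, the variance relative to the change contrast is (1 − ρ²)/(2(1 − ρ)), which is 0.75 at an assumed ρ of 0.5 and 0.70 to 0.85 for ρ from 0.4 to 0.7. That gain comes from T0, not from sex or age.

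The cost is one line of model specification and, for the first option, one extra parameter per covariate and post-baseline occasion. No new data are needed, and completed recruitment is no obstacle.

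### Randomisation is stratified by treatment centre and sex, but the primary model leaves centre out and names sex only as an example; the effect on the standard error is nil to slightly conservative

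*Protocol article*

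**What the plan says.** Under Design, the protocol article states: "Stratified randomization by treatment center and sex will be conducted". Random number tables are made for each centre, divided by sex, with blocks of 12 per centre split into six men and six women. The reason given for using centre is that centres differ in size and arm numbers should stay roughly equal even in small ones. The article does not say that centre predicts outcome.

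Under Statistical analyses, the model has two levels, time and participant, with T0 as the reference category. On covariates it says that "several covariates will be included in the model (e.g., sex and age"), which is an open list. Centre is neither a level nor a named covariate. It gets a sentence of its own: "The existence of an effect of HIV treatment center will be investigated exploratory".

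Under Participants, 23 centres take part and at least 200 participants are sought. No intracluster correlation is given; the term appears only in the list of abbreviations.

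**The concern.** A variable used to restrict the randomisation normally belongs in the model that estimates the treatment effect. Stratifying makes the arms alike on that variable. If the variable also predicts the outcome, a model that omits it leaves its variance in the residual and reports a standard error larger than the design produces. Confidence intervals are then a little too wide and some power is lost.

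This is not a detail that a condensed article leaves to an analysis plan. The article itself fixes the levels of the model and assigns centre an exploratory role. Elsewhere (Ethical precautions; Demographic variables and other information) it firmly commits to covariates that arise after randomisation, namely referral, medication and treatment received. One of the two randomisation factors gets no such commitment and the other appears only as an example.

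**Working it through.** **1. The plan's own figure.** Inputs from Sample size and Statistical analyses: effect size 0.50, two-sided alpha .05, power .80. The two-sample t-test solution is 63.77, rounded up to 64 per group (power at 64: 0.801), which matches "both groups should consist of 64 participants who complete the four measurements". Allowing for 15% dropout, 64/0.85 = 75.3 per group, against the stated 75, a rounding difference only. Centre plays no part in this calculation, so the sample size is not in question.

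**2. If the effect were a comparison of single post-test scores.** Let ρ be the share of outcome variance that lies between centres (assumed). With unit variance and n per arm, a model without centre reports SE = √(2/n). If the arms are balanced within centres, the centre part cancels and the true SE is √(2(1−ρ)/n). The ratio of reported to true is 1/√(1−ρ), and the actual two-sided alpha is 2Φ(−1.96/√(1−ρ)). With n = 64 and the normal approximation:

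| ρ (assumed) | reported/true SE | actual alpha | power, centre ignored | power, centre in model |
|---|---|---|---|---|
| 0.02 | 1.010 | 0.048 | 0.810 | 0.815 |
| 0.05 | 1.026 | 0.044 | 0.814 | 0.827 |
| 0.10 | 1.054 | 0.039 | 0.820 | 0.847 |

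This assumes ideal balance. In fact 23 × 2 = 46 strata share 200 participants, 200/46 = 4.3 each, fewer than the within-sex block of 6, so many blocks stay incomplete. A simulation used 23 unequal centres, blocks of 6 within centre and sex, 85% men (assumed), N = 128 and 8,000 runs per setting, with least squares standing in for the multilevel model. It gave ratios of 1.00–1.01, 1.02–1.03 and 1.03–1.04 at the same three values of ρ.

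**3. The effect that the stated model points to.** With T0 in the outcome and as the reference category, the natural effect is condition by time, a change from T0. Write a score as u (centre, constant) + v (centre at that time) + p (participant) + e. In the change from T0, u and p drop out:

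change = (v₁ − v₀) + (e₁ − e₀) + treatment effect.

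- *Centre effect constant over time* (v = 0). In the same simulation, analysing change at ρ = 0.05 and 0.10, reported/empirical SE was 0.98–1.00 and the null rejection rate 0.050–0.053. Simulation error at 8,000 runs is about 1/√16,000 = 0.8% on the ratio and √(0.05 × 0.95/8,000) = 0.002 on the rejection rate, so there is no consistent bias. Adding only a centre random intercept left the condition-by-time SE unchanged (ratio 0.999–1.000).
- *Centres differ in change over time* (v ≠ 0). Now ρ in step 2 is the centre share of the variance of change. At 0.05 and 0.10 the formula gives 1.026 and 1.054. A separate check with centre-by-time variances of 0.05 and 0.10 gave about 3% and 6%. The exact value moves with how that variance is expressed and with how complete the blocks are, so 3% to 6% is an order of magnitude.

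**4. What form the adjustment should take.** There are 128/23 = 5.6 to 200/23 = 8.7 participants per centre. In the post-score simulation at N = 128, 22 fixed centre dummies gave power of 0.775 against 0.810 without centre at ρ = 0, 0.786 against 0.803 at 0.05, and 0.813 against 0.817 at 0.10. A random intercept on post scores, with its variance treated as known, did not raise the empirical SE at any ρ from 0 to 0.10 (ratio 0.99–1.00).

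**The case against.** The strongest reply is that nothing in the article suggests that centre matters for outcome. Centres screen and refer; the programme runs on a website and support comes by telephone from study coaches. Centre was used to balance numbers, not because it is prognostic. This stands as a reason to expect a small effect. It does not settle the matter: the Procedure section lets some centres pre-screen with the HADS and others with the PHQ-2, so referral routes differ, although all participants then pass the same PHQ-9 screen.

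Three stronger readings are tempting, and the document does not support them.

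- A reader might infer that the standard error is wrong whatever the centre effect looks like. Step 3 shows otherwise: a constant centre effect cancels, and only centre differences in change matter.
- A reader might infer that centre will enter the primary model if the exploratory look finds an effect, making the model data-dependent. The article states no such rule. It simply does not say what follows from that look.
- A reader might take chance imbalance of women between arms, which sparse strata allow, as a case for adding centre. That imbalance concerns sex, which is already named as a covariate, though only as an example.

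**Conclusion.** The mismatch between design and analysis is real and stands in the text: centre is a stratification factor, yet the stated model omits it and only explores it, and sex has no firm commitment. Its size is minor. For the condition-by-time effect, the standard error is essentially correct if the centre effect is constant over time. It is too large by about 3% to 6% if the centre-by-time variance is 5% to 10% of total variance. That range is an assumption, since the article gives no figure. The error runs in the conservative direction, so a significant result would not be undermined. The cost is a slightly wide interval and a little power: under ideal balance, 0.820 against 0.847 when centre holds 10% of the variance of the outcome analysed.

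**What to change.** State in the analysis section that every multilevel model of condition, for primary and secondary outcomes, includes both stratification factors whatever the exploratory analysis of centre shows:

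- sex as a fixed effect, with sex by time;
- treatment centre as a random effect with a centre-by-time component. A centre random intercept is enough only if the effect is estimated on post scores adjusted for baseline.

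Do not use 22 fixed centre dummies. Keep only the centre-by-condition interaction exploratory. If the full analysis plan already says this, the article's sentence on centre should be brought into line with it.

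The cost is one sentence. Both variables are already used for the randomisation, and completed recruitment is no obstacle because no new data are needed. The downside is one or two extra variance components which, with about 6 to 9 participants per centre, may be estimated near zero. A simpler fallback model for that case should be named in advance.
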